### ***Adverse Event***

All AEs will be coded using the Medical Dictionary for Regulatory Activities (MedDRA). The severity of AEs will be graded according to the NCI-CTCAE Version 5.0 Toxicity Rating Scale. AEs will be summarized by preferred term (PT) and system organ class (SOC) with their severities and relationship to the study drug described.

Analysis of AEs will include, but is not limited to:

Version No.: 4.2

- All adverse events (AEs);
- Serious adverse events (SAEs);
- Treatment-emergent adverse events (TEAEs);
- Treatment-related adverse events (TRAEs);
- Immune-related adverse events (irAEs);
- AEs leading to treatment discontinuation;
- AEs leading to death;
- AEs of special interest.

### ***Tolerability***

The tolerability of subjects to the investigational products will be evaluated by the number of subjects with dose interruption, delay, and discontinuation. Reasons for dose interruption, delay, and discontinuation will be listed, and descriptive statistical analysis will be performed on the frequency of dose interruption, delay and discontinuation by cohort.

### ***Laboratory Abnormalities***

Laboratory results will be graded according to NCI-CTCAE Version 5.0. Parameters that cannot be graded will be classified as decreased/normal/increased according to the normal range of laboratory tests.

Test values for each laboratory test (e.g., hematology, serum chemistry, etc.) will be listed by laboratory parameter, subject, and dose level. Then, the frequency of obvious laboratory abnormalities (Grade 3 or 4 laboratory test abnormalities judged per the NCI-CTCAE Version 5.0) will be described by parameters, number of treatment cycles and dose levels; and the frequency of all laboratory abnormalities will be described by parameter, worst grade (according to the NCI-CTCAE Version 5.0), and dose level.

The obvious laboratory abnormalities (Grade 3 or 4 laboratory test abnormalities judged by the NCI-CTCAE Version 5.0) will be listed. For the parameters that can be categorized using the CTCAE Version 5.0, laboratory data can be summarized by changes in grade as listed in the tables. The parameters that could not be categorized according to the CTCAE Version 5.0 are divided into 3 groups (decreased/normal/increased) according to the normal range, and the data will be listed to statistically analyze the frequency of occurrence.

***Other Safety Data (Physical Examination, ECG and Vital Signs)***

All ECG parameters, including the QT interval corrected according to the Fridericia method (QTc interval) for each subject, will be listed, and descriptive statistical analysis will be performed on the change from baseline for each parameter by dose level and evaluation time. Dose groups as well as correlations of changes in PK parameters (e.g.,  $C_{max}$ ,  $AUC_{0-t}$ ) and QTc will be presented graphically.

Blood pressure, pulse, respiratory rate, body temperature, and body weight will be listed for all subjects, and changes from baseline for each value will be presented and statistically described.

All physical examination findings will be listed.

**Efficacy Endpoints**

The analysis of efficacy endpoints will be performed based on the EAS, and PFS and OS will be analyzed based on the SS. The 95% CIs calculated by Clopper Pearson method will be reported by dose group for individual proportion (CBR); the parameters (including median and 95% CIs) of time-related events (PFS and OS) calculated by the Kaplan-Meier method will be reported by dose group;

The specific analytical contents and analytical methods will be detailed in the SAP.

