## 4 STUDY DESIGN

### OVERALL STUDY DESIGN

This study is an open-label, Phase 2, multicenter clinical study to evaluate the efficacy and safety of KN026 in combination with KN046 in subjects with HER2-positive solid tumors.

The study will include:

Three different cohorts of HER2-positive solid tumors treated with KN026 30 mg/kg Q3W (loading dose on C1D1 and D8) in combination with KN046 5 mg/kg Q3W:

- HER2-positive gastric/gastroesophageal junction cancer (GC/GEJ), n = 30 to 60;
- HER2-positive breast cancer (BC), n = 30 to 36;
- Other HER2-positive solid tumors, n = 20 to 26.

HER2-positive is defined as follows:

- HER2 IHC3+ (ASCO/CAP 2018; Wolff et al, 2018); **or**
- HER2 gene amplification (ISH+: HER2/CEP17 ratio > 2 or HER2 gene copy number > 6; or NGS: HER2 gene copy number > 6).

All subjects will be required to submit slides for central laboratory review of HER2 status at screening. Subjects who have received HER2-targeted therapies such as trastuzumab should provide tumor tissue samples collected after failure of HER2-targeted therapy for determination of HER2-positive status.

The study is divided into a screening period (Day -28 to -1), a treatment period, the end-of-treatment (EOT) follow-up visit, a 30-day safety follow-up visit, a 90-day safety follow-up visit, and a survival follow-up visit.

Subjects will undergo tumor imaging assessments at screening and every 6 weeks ( $\pm$  7 days) after the dose of study drug. After 48 weeks, the frequency of imaging assessments will be adjusted to every 12 weeks ( $\pm$  7 days) until disease progression per RECIST 1.1, initiation of a new anti-tumor therapy, or subject withdrawal of consent, whichever occurs first. When an objective response defined in RECIST 1.1 occurs, confirmation by imaging should be performed no earlier than 4 weeks and no later than 8 weeks.

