### Safety Set

The safety set (SS) includes all subjects who have received at least 1 full or partial dose of KN026 and/or KN046. Subjects will be categorized according to the treatment groups planned in the protocol. All raw data will be counted using SS, which will be the default analysis set used for all analyses unless otherwise noted.

Subjects who fail screening will be only listed, but not summarized for analysis.

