### Efficacy Analysis Set

The Efficacy Analysis Set (EAS) includes all subjects who have received at least 1 full or partial dose of KN026 and/or KN046 and have at least one postbaseline tumor imaging evaluation. This analysis set will be used for supportive analyses.

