## **ANALYSIS OF THE PRIMARY ENDPOINT**

ORR and DOR: The 95% CIs calculated by Clopper Pearson method will be reported by cohort based on the SS; and the parameters of the time-related event (DOR) will be calculated using the Kaplan-Meier method by cohort.

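### Section 9.6.2 puts CBR on the supportive-only set that excludes unscanned subjects, and reports CBR, PFS and OS by dose group in a trial with one regimen and three cohorts

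*Protocol*

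**What the plan says.** **Analysis set.** Section 9.6.2 (Efficacy Endpoints) reads: "The analysis of efficacy endpoints will be performed based on the EAS, and PFS and OS will be analyzed based on the SS". Only PFS and OS are exempted, so CBR is on the EAS. Section 9.3.2 admits a dosed subject to the EAS only if they "have at least one postbaseline tumor imaging evaluation", and adds: "This analysis set will be used for supportive analyses". Section 9.3.1 defines the SS as all dosed subjects, "which will be the default analysis set used for all analyses unless otherwise noted". For the primary endpoint, Section 9.5 says: "The 95% CIs calculated by Clopper Pearson method will be reported by cohort based on the SS".

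**Reporting unit.** In Section 9.6.2 the "time-related events (PFS and OS) calculated by the Kaplan-Meier method will be reported by dose group", and the CBR interval has the same reporting unit. Section 4.1 describes "Three different cohorts of HER2-positive solid tumors treated with KN026 30 mg/kg Q3W", all three in combination with the same KN046 schedule.

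**The concern.** There are two separate problems in one section.

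First, Section 9.6.2 makes the EAS the main set for CBR, a role that Section 9.3.2 does not give it. Entry to the EAS depends on something that happens after treatment starts. A subject who dies, withdraws, is lost to follow-up or starts a new therapy before any scan leaves the CBR denominator, yet stays in the ORR denominator. CBR is then favoured by construction. The gap between CBR and ORR, which should be the share with stable disease of at least 24 weeks, no longer has that meaning.

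Second, the trial has one regimen, so it has one dose group. Read as written, CBR, PFS and OS would each be a single estimate over gastric, breast and other tumors. Such a median would depend on how many subjects each cohort enrolled, and it could not be set beside the ORR and DOR reported by cohort.

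**Working it through.** **Inputs**
- CBR is CR, PR or SD of at least 24 weeks (Section 3.2.2). Each category needs a post-baseline assessment, so an unscanned subject cannot count as a benefit.
- Planned cohort sizes (Section 9.2): gastric 30–60, breast 30–36, other 20–26.
- Share of dosed subjects without a scan in this trial: not stated, so it is an assumption.

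**The plan's own figure.** The precision table in Section 9.2 gives 12/30 = 40% with interval (22.7%, 59.4%). The exact Clopper-Pearson calculation returns the same limits. This case is the base for the illustration.

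**Formula.** Let n be dosed subjects, m those without a scan and x those with clinical benefit.
- CBR on the SS = x/n.
- CBR on the EAS = x/(n − m) = (x/n) / (1 − m/n).

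The second is never smaller than the first, and it is larger whenever m ≥ 1 and x ≥ 1.

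**Range for m/n from the earlier studies in Sections 1.3.3 and 1.4.3**
- KN026-CHN-I-001: 62 assessed of 63 treated, so 1/63 = 1.6% unassessed. 40/(62/63) = 40.6%.
- KN046-CHN-001: 75 evaluable of 88, so 13 were not evaluable. Of 33 still on treatment, 29 were evaluable, so 33 − 29 = 4 of the 13 were still on treatment. At most 13 − 4 = 9 had left treatment unevaluated: 9/88 = 10.2%, and 40/(1 − 0.102) = 44.6%.
- KN046-IST-02: 7 + 11 + 7 = 25 evaluable of 32, so 7/32 = 22% not evaluable. 40/(25/32) = 51.2%.

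**Effect at planned cohort sizes (assumed 40% benefit on the SS)**

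| n | x | m | CBR on SS (95% CI) | CBR on EAS (95% CI) |
|---|---|---|---|---|
| 30 | 12 | 1 | 40.0% (22.7, 59.4) | 41.4% (23.5, 61.1) |
| 30 | 12 | 3 | 40.0% (22.7, 59.4) | 44.4% (25.5, 64.7) |
| 30 | 12 | 7 | 40.0% (22.7, 59.4) | 52.2% (30.6, 73.2) |
| 60 | 24 | 6 | 40.0% (27.6, 53.5) | 44.4% (30.9, 58.6) |
| 60 | 24 | 13 | 40.0% (27.6, 53.5) | 51.1% (36.1, 65.9) |

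**Comparability with ORR.** Suppose n = 30, m = 3, and all 12 subjects with benefit are responders, so that nobody has long stable disease. ORR on the SS is 12/30 = 40.0% and CBR on the EAS is 12/27 = 44.4%. The 4.4-point gap would look like durable stable disease that no subject had.

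**Reporting unit.** Taken literally, one dose group holds all 80 to 122 subjects. The gastric share could run from 30/(30 + 36 + 26) = 33% to 60/(60 + 30 + 20) = 55%, depending on enrolment alone.

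**The case against.** **Who leaves the denominator.** A reader might infer that anyone who stops treatment before the week-6 scan drops out of CBR. The protocol does not support that. Footnote 13 of the Study Flow Chart and Sections 5.3.1, 7.1.3 and 7.2.2.3 keep subjects who stop for toxicity or clinical deterioration in tumor imaging. If those rules are followed, such subjects are scanned and stay in the EAS. Early death, withdrawal, loss to follow-up or new therapy before any scan remain as routes out. This objection narrows the mechanism but does not remove it.

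**Size.** A reader might take the raw evaluable shares, 75/88 and 25/32, and conclude that a 40% CBR would be reported as 47% to 51%. The documents do not support that as an estimate. Both shares come from data cut-offs, and 4 of the 13 unevaluable subjects in KN046-CHN-001 were still on treatment. In KN046-IST-02 the seven evaluable subjects with other gastrointestinal tumors are described as second line or later, while the ten enrolled are not limited by line, so numerator and denominator may not match. The low end is also uncertain. KN026-CHN-I-001 reports 62 assessed, but its 14 confirmed and unconfirmed responses and 27.5% ORR imply about 14/0.275 = 51 subjects. No single rate can be relied on.

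**Pooling.** A reader might infer that the plan has decided to pool the survival curves across tumors. It never says so. Dose-level wording also appears in Sections 9.4 and 9.6.1, which suggests text left over from a dose-escalation study. Design, sample size, primary analysis, tolerability and immunogenicity are all by cohort. The likely intent is by cohort, but Section 9.6.2 does not say it.

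**Left to the SAP.** Section 9.6.2 defers detailed methods to the SAP, and the SS is the default only where nothing else is noted. But Section 9.6.2 has itself fixed the set and the reporting unit. An SAP that used the SS and cohorts would contradict it, and one that followed it would carry the error forward.

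**Conclusion.** The point holds for CBR and for the reporting unit. As written, Section 9.6.2 conflicts with the supportive role in Section 9.3.2, and CBR gets a different denominator from ORR. The direction is certain: CBR can only be raised. The size is not known. Assuming 2% to 10% of dosed subjects have no scan, a 40% CBR on the SS reads about 41% to 45% on the EAS. About 51%, at 22% unscanned, is a loose upper bound, and the effect is zero if everyone is scanned.

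The dose-group wording does not fit a one-regimen trial. Its literal result is one combined CBR, PFS and OS across three tumor cohorts, although carry-over from a template is the likelier explanation.

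A must-fix rating would go too far. CBR, PFS and OS are descriptive secondary endpoints, and no hypothesis test or decision rule rests on them. ORR, PFS and OS are already on the SS, and DOR concerns responders, who have all been scanned. This is a should-fix point.

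**What to change.** In Section 9.6.2:
1. Analyse CBR on the SS, counting dosed subjects with no post-baseline scan as having no clinical benefit. Keep the EAS result as supportive, as Section 9.3.2 already intends.
2. Replace the dose-group reporting unit with cohort for CBR, PFS and OS, to match Section 9.5.

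Reporting by cohort still combines first-line and later-line gastric subjects and leaves a mixed cohort of other tumors. It aligns the secondary endpoints with the primary analysis but does not make each cohort homogeneous.

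The cost is two wording changes, with no new data, visits or subjects. The reported CBR will be somewhat lower wherever any subject lacks a scan.

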**Pharmacokinetic Endpoints**

The concentration-time curves will be plotted for subjects by measured plasma concentrations of KN046 and KN026 and the actual blood collection time points, and PK parameters will be calculated using a non-compartmental model; the mean (arithmetic mean and geometric mean) concentration-time curves will be plotted by measured plasma concentrations of KN046 and KN026 and the scheduled blood collection time points. Concentrations below the LLOQ will be recorded as zero and included in the calculation of PK parameters. Missing sample information will be recorded, but missing samples will not be included in the calculation of PK parameters.

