14 Subjects who do not have a bone scan within 90 days prior to the first dose will be required to perform bone scan at screening. Subsequently, bone scan should be performed only if clinically indicated. For new lesions suggested by the bone scan, CT/MRI examination is required to determine whether it is metastatic, and oncology evaluation will be performed according to RECIST 1.1 criteria;

15 The duration of each infusion for the first 6 doses of KN046 should be no less than 120 minutes; if no infusion-related adverse events occur, the subsequent infusion time may be adjusted to 90-120 minutes; after the end of each infusion of KN046, the subject should be observed at the study site for at least 2 hours. The first infusion time of KN026 should be 90 minutes ( $\pm$  15 minutes). If no infusion-related AEs occurred during the first infusion, the subsequent infusion time could be adjusted to 60 minutes (45 to 75 minutes); after the end of each dose of KN026, the subject should be observed at the study site for at least 2 hours. If KN046 and KN026 are administered on the same day, KN026 should be administered first and then KN046 after 2 hours of the end of infusion.

**Table 2 Study Flow Chart: Pharmacokinetic and Immunogenicity Sample Collection Form of KN046 and KN026, and ECGs Performed Concurrently with PK Blood Sampling**

| Week | Time                                       | KN046 PK Sample | KN046 ADA Sample | KN026 PK Sample | KN026 ADA Sample | ECGs Performed Concurrently with PK Blood Sampling |
|------|--------------------------------------------|-----------------|------------------|-----------------|------------------|----------------------------------------------------|
| 1    | 0 h (pre-dose of KN046 or KN026) (-60 min) | 3.5 mL          | 3.5 mL           | 3.5 mL          | 3.5 mL           | X                                    |
| 1    | End of KN046 or KN026 infusion (+ 30 min)  | 3.5 mL          |                  | 3.5 mL          |                  | X                                    |
| 2    | 0 h (pre-dose of KN026) (-60 min)          |                 |                  | 3.5 mL          | 3.5 mL           |                                                    |
| 2    | End of KN026 infusion (+ 30 minutes)       |                 |                  | 3.5 mL          |                  |                                                    |

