| 4    | 0 h (pre-dose of KN046 or KN026) (-60 min) | 3.5 mL          | 3.5 mL           | 3.5 mL          | 3.5 mL           |                                                    |
| 4    | End of KN046 or KN026 infusion (+ 30 min)  | 3.5 mL          |                  | 3.5 mL          |                  |                                                    |
| 7    | 0 h (pre-dose of KN046 or KN026) (-60 min) | 3.5 mL          | 3.5 mL           | 3.5 mL          | 3.5 mL           |                                                    |
| 7    | End of KN046 or KN026 infusion (+ 30 min)  | 3.5 mL          |                  | 3.5 mL          |                  |                                                    |
| 10   | 0 h (pre-dose of KN046 or KN026) (-60 min) | 3.5 mL          | 3.5 mL           | 3.5 mL          | 3.5 mL           | X                                    |
| 16   | 0 h (pre-dose of KN046 or KN026) (-60 min) | 3.5 mL          | 3.5 mL           | 3.5 mL          | 3.5 mL           |                                                    |
| 22   | 0 h (pre-dose of KN046 or KN026) (-60 min) | 3.5 mL          | 3.5 mL           | 3.5 mL          | 3.5 mL           |                                                    |
| 31   | 0 h (pre-dose of KN046 or KN026) (-60 min) | 3.5 mL          | 3.5 mL           | 3.5 mL          | 3.5 mL           |                                                    |
| 40   | 0 h (pre-dose of KN046 or KN026) (-60 min) | 3.5 mL          | 3.5 mL           | 3.5 mL          | 3.5 mL           |                                                    |
| 49   | 0 h (pre-dose of KN046 or KN026) (-60 min) | 3.5 mL          | 3.5 mL           | 3.5 mL          | 3.5 mL           |                                                    |

|                                                                                                                                                                                                                                                                                           |                                            |        |        |        |        |  |

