|-------------------------------------------------------------------------------------------------------------------------------------------------------------------------------------------------------------------------------------------------------------------------------------------|--------------------------------------------|--------|--------|--------|--------|--|
| 58                                                                                                                                                                                                                                                                                        | 0 h (pre-dose of KN046 or KN026) (-60 min) | 3.5 mL | 3.5 mL | 3.5 mL | 3.5 mL |  |
| 67                                                                                                                                                                                                                                                                                        | 0 h (pre-dose of KN046 or KN026) (-60 min) | 3.5 mL | 3.5 mL | 3.5 mL | 3.5 mL |  |
| EOT                                                                                                                                                                                                                                                                                       |                                            | 3.5 mL | 3.5 mL | 3.5 mL | 3.5 mL |  |
| 30-Day Safety Follow-up Visit                                                                                                                                                                                                                                                             |                                            | 3.5 mL | 3.5 mL | 3.5 mL | 3.5 mL |  |
| 90-Day Safety Follow-up Visit                                                                                                                                                                                                                                                             |                                            | 3.5 mL | 3.5 mL |        |        |  |

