As of January 20, 2020, 35 subjects received at least one postbaseline response evaluation and were included in the efficacy analysis. The results showed 1 confirmed CR, 2 confirmed PR, 4 unconfirmed PR, 15 SD, and 20 PD. The objective response rate (CR + PR) was 16.7% and the disease control rate (CR + PR + SD) was 52.4%. As of the cut-off date, 8 evaluable subjects were still receiving KN046 treatment.

After administration of 3 mg/kg (n = 3), KN046 showed linear elimination in humans with half-lives ranging from 4.4 to 7.3 days (mean 6.2 days) and trough concentrations ranging from 4.6 to 6.8 µg/L (mean 5.4 µg/L) on Day 15. After administration of 5 mg/kg (n = 6), KN046 showed linear elimination in humans with half-lives ranging from 5.2 to 11.3 days (mean 8.0 days) and trough concentrations ranging from 5.9 to 16.2 µg/L (mean 12.8 µg/L) on Day 15

- 2) KN046-CHN-001 was a Phase 1a/1b study in Chinese subjects conducted at the Sun Yat-sen University Cancer Center. As of January 20, 2020, 88 subjects were enrolled in the study, including 1 mg/kg Q2W (n = 1), 3 mg/kg Q2W (n = 30), 5 mg/kg Q2W (n = 45), 5 mg/kg Q3W (n = 6), and fixed dose of 300 mg Q3W (n = 6). Subjects received KN046 for a median exposure time of 12 weeks (range: 2 to 54 weeks). Of these, 45 (51.1%) subjects had an exposure time of more than 12 weeks, 20 (22.7%) subjects had more than 24 weeks, 12 (13.6%) subjects had more than 36 weeks, and 2 (2.3%) subjects had more than 48 weeks. Thirty-three subjects are still receiving study treatment. A total of 55 subjects have discontinued study treatment, including: 1) 36 subjects due to disease progression; 2) 5 subjects due to AEs; 3) 3 subjects due to death; 4) 2 subjects due to lost to follow-up; and 5) 9 subjects due to other reasons. The subjects enrolled in the Phase 1 study in China were mainly patients with advanced solid tumors. There were no DLT events during the dose escalation phase and the maximum tolerated dose was not reached at 5 mg/kg Q2W, therefore 5 mg/kg Q2W was considered as the RP2D. As of the cut-off date, 74 (84.1%) of 88 subjects experienced TRAEs, 9 (10.2%) experienced TRAEs of Grade 3 or above, and 4 (4.5%) experienced treatment-related SAEs. Forty (45.5%) subjects experienced irAEs, of which 4 (4.5%) were Grade 3. Similar to the results of the KN046-AUS-001 study, TRAEs and irAEs showed no dose dependence during the dose escalation phase. The most common TRAEs

Version No.: 4.2

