#### Rationale for Dose Selection of KN046

The pre-specified dose of KN046 for this study is 5 mg/kg Q3W. The rationale for dose selection was mainly based on the safety and preliminary efficacy data from the KN046-AUS-001 study (first-in-human study of KN046) and KN046-CHN-001 study (first-in-China study of KN046). The safety evaluation at 5 mg/kg Q2W has been completed in KN046-AUS-001 and the safety evaluations at 5 mg/kg Q2W and Q3W have been completed in KN046-CHN-001. KN046 was generally well tolerated by the subjects. Based on the *ex vivo* release data of IL-2 from tumor patients in KN046-CHN-001 clinical study and corresponding KN046 drug concentration data, a PK (pharmacokinetic)/PD (pharmacodynamic) model was constructed to explore the correlation between drug concentration and *ex vivo* release of IL-2.

As of June 24, 2019, *in vitro* releasing data of IL-2 were obtained from 16 subjects, and a PK/PD model was constructed using R, with the model equation as:

$$E(C) = E0 - \frac{Imax \cdot (E0 - 1) \times C}{IC50 + C}$$

The corresponding Ctrough\_targets (IC95) were estimated from the point estimate of IC50 (138 ng/mL) and the upper limit of 95% CI (457 ng/mL), respectively. The corresponding Ctrough\_targets were 2,629 ng/mL and 8,683 ng/mL, respectively. Ctrough\_target was placed into the 3 mg/kg Q2W, 5 mg/kg Q2W and the fitted 5 mg/kg Q3W concentration-time curve. Since more than 75% of the dosing interval of 5 mg/kg Q3W per cycle was above Ctrough\_target, 5 mg/kg Q3W may be suitable for KN046 combination therapy.

KN046-IST-02 study has demonstrated that KN026 20 mg/kg Q2W + KN046 3 mg/kg Q2W is a safe and effective dose. Based on the data from Phase 1 studies of KN026 and KN046 and PK/PD study results, and considering that dosing every three weeks is more convenient in clinical practice, the dose of KN026 30 mg/kg Q3W + KN046 5 mg/kg Q3W is selected for this study. The safety data from the dose group KN026 30 mg/kg Q3W + KN046 5 mg/kg Q3W will be provided as further support before the subjects are enrolled in this study.

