**Correlation between Pharmacokinetic and Clinical Efficacy Variables**

Logistic regression analysis will be conducted on AUC ( $AUC_{0-t}$ ,  $AUC_{inf}$ , and  $AUC_{last}$ ),  $C_{trough}$  and  $C_{max}$  versus clinical efficacy variables (ORR, CBR, PFS rate, and OS rate).

Data for AUC can be derived from the results of population pharmacokinetic analysis.

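### Section 9.6.3 requires non-compartmental PK parameters, but the sampling schedule gives at most a peak and a trough per dosing interval; AUC and AUCinf need population PK as the stated source.

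*Protocol*

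**What the plan says.** Section 9.6.3 fixes the method for KN046 and KN026 alike: "PK parameters will be calculated using a non-compartmental model". It names no integration rule. Values below the quantification limit enter as zero.

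The PK sampling table (Table 2) provides:

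- **Weeks 1, 4 and 7, both drugs:** a pre-dose sample and one post-dose sample, "End of KN046 or KN026 infusion (+ 30 min".
- **Week 2, KN026 only (the Day 8 dose):** a pre-dose and an end-of-infusion sample.
- **Weeks 10, 16, 22, 31, 40, 49, 58 and 67:** pre-dose samples only.
- **After the last dose:** EOT and 30-day samples for both drugs, and a 90-day sample for KN046 only.

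The exposure metrics are used in three places:

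- Section 3.2.2 lists Cmax,ss, AUCss, Ctrough,ss and Cavg,ss, to be correlated with efficacy and with QTc and LVEF.
- Section 9.6.1 (other safety data) plots PK parameters such as Cmax and AUC0-t against QTc.
- Section 9.6.4 regresses efficacy variables on AUC0-t, AUCinf, AUClast, Ctrough and Cmax, and adds: "Data for AUC can be derived from the results of population pharmacokinetic analysis".

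**The concern.** The stated method does not fit the stated schedule. Non-compartmental AUC is computed from the observed points, and AUCinf also needs a slope from the terminal phase. Here an interval has a peak and a trough, or only a trough.

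The exposure-response analyses are secondary endpoints and depend on differences in AUC between subjects. An AUC error that grows with clearance would inflate the values and also shrink those differences. Section 9.6.4 offers a way out through population PK, but as a permission (*can*) set against an instruction (*will*) in 9.6.3. It also appears under a heading confined to efficacy. The protocol does not say which statement prevails, or where the AUC for the QTc and LVEF correlations comes from.

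**Working it through.** The protocol gives no AUC figure to reproduce, so the check is a count of usable intervals followed by a bias calculation.

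**Usable intervals.** An interval needs an end-of-infusion sample and a closing trough.

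- KN046 has three: Weeks 1–4, 4–7 and 7–10.
- KN026 has four: Weeks 1–2, 2–4, 4–7 and 7–10.
- Each has exactly two post-dose points. Later sampled intervals have only the trough.

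**Inputs.** The interval τ is 21 days ("The pre-specified dose of KN046 for this study is 5 mg/kg Q3W"). KN046 half-lives at 5 mg/kg come from section 1.4.3: "half-lives ranging from 5.2 to 11.3 days (mean 8.0 days", n = 6, in a previous study. Let k = ln 2 / half-life, let C0 be the end-of-infusion concentration, and assume mono-exponential decline.

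- True AUC over the interval: C0(1 − e^(−kτ))/k
- Linear trapezoid: τ·C0(1 + e^(−kτ))/2
- Ratio, linear to true: (kτ/2)/tanh(kτ/2)
- Log trapezoid: equal to the true AUC under this shape
- Share of single-dose AUCinf beyond the trough: e^(−kτ)

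| Half-life (days) | kτ/2 | Linear / true | Linear bias | Log bias | Share of AUCinf beyond Day 21 |
|---|---|---|---|---|---|
| 5.2 | 1.3996 | 1.5810 | +58% | 0 | 6% |
| 8.0 | 0.9098 | 1.2618 | +26% | 0 | 16% |
| 11.3 | 0.6441 | 1.1346 | +13% | 0 | 28% |

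**Compression under the linear rule.** Take two subjects with equal C0 and half-lives of 11.3 and 5.2 days.

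- True AUCs are 11.81 and 7.05 C0·days, a difference of 68% (11.81/7.05 = 1.68).
- Linear AUCs are 13.40 and 11.14 C0·days, a difference of 20% (13.40/11.14 = 1.20).

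**Sensitivity to a distribution phase.** The protocol has no distribution-phase data, so these values are assumptions: 30% to 50% of C0 declines with a half-life of 0.5 to 1.5 days, and the rest with the half-lives above.

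- Linear AUC over 21 days is 41% to 179% too high.
- Log AUC over 21 days is 14% to 50% too high.
- AUCinf extrapolated from the two-point slope is 6% to 46% too high with the log rule and 24% to 168% too high with the linear rule.
- As an example, with a true terminal half-life of 8.0 days, a 30% share and a 1.5-day distribution half-life, the peak-to-trough slope implies 6.7 days.

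Two points determine a line exactly and cannot show whether that line is the terminal phase.

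**Samples after the last dose.** Relative to the end-of-infusion value, KN046 at the 8.0-day half-life is 2^(−30/8) = 7.4% at 30 days and 2^(−90/8) = 0.04% at 90 days. Over the half-life range the 30-day value is 1.8% to 15.9%. The quantification limit is not stated, and values below it are set to zero. If the last dose is at Week 10 or later, its own peak was not sampled.

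**KN026.** No human half-life is given. At an assumed 8 days, linear bias is about 3% over the 7-day interval, 12% over the 14-day interval and 26% over 21 days. At an assumed 5 to 20 days, the 21-day bias runs from +62% to +4%. The shorter first interval does not help AUCinf: at 8 days, 2^(−7/8) = 55% of it lies beyond Day 8.

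**The case against.** There are four fair objections.

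- **The percentages need a linear rule.** The protocol does not name one, and the SAP, which is not shown, would ordinarily fix it. This stands. A reader might infer that AUC in this trial will be overstated by 13% to 58%; the document does not support that as a flat statement. What remains is that the log rule removes the bias only for mono-exponential decline.
- **Population PK is already allowed.** A reader might infer that the exposure-efficacy results will be biased. Section 9.6.4 rules that out as a certainty, because AUC may come from a model. The permission is optional, however. It disagrees with the instruction in 9.6.3, and it is not carried to the QTc and LVEF correlations.
- **There are later samples.** A reader might infer that AUCinf is strictly not estimable. The EOT, 30-day and KN046 90-day samples prevent so absolute a claim. They are unlikely to give a usable terminal slope in practice, so *not reliably estimable* is the right strength.
- **The stakes are limited.** These are secondary analyses in a descriptive single-regimen Phase 2 trial, and ORR, DOR and the safety summaries are untouched. This stands and limits the weight of the point.

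Deferral to the SAP does not settle the matter. The protocol prescribes a method that its own schedule cannot serve, and a SAP that relied on population PK would depart from 9.6.3 as worded.

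**Conclusion.** The point holds in conditional form. Followed as written, section 9.6.3 yields no reliable AUCinf for either drug, and AUC0-t, AUCss and Cavg,ss that rest on two samples. For KN046 over 21 days, a linear trapezoid would overstate AUC by about 13% to 58% (26% at the mean half-life) and would narrow true differences between subjects. That size rests on mono-exponential decline and on half-lives from six subjects; it falls to zero with a log rule under the same shape. For KN026 the size is unknown, and it is smaller in the shortened first intervals. The protocol already contains the remedy as an option, so the defect is a conflict between two sections about the source of AUC and a gap for the safety correlations.

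**What to change.** Three wording changes:

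1. In 9.6.3, limit non-compartmental reporting to observed end-of-infusion and trough concentrations.
2. In 9.6.3 and 9.6.4, state that AUC, Cavg,ss and the other steady-state exposure metrics *will* be individual estimates from population PK. Apply this to the efficacy correlations and to the QTc and LVEF correlations in 3.2.2 and 9.6.1.
3. Take AUCinf from the model, or drop it from the regressors in 9.6.4.

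The change adds no samples to the schedule, but it has a cost. Population PK modelling becomes mandatory for both drugs, and the protocol describes an existing population model for KN026 only (section 2.1.1). For KN046 it describes a PK/PD model and a fitted concentration curve (section 2.1.2). Individual estimates will also depend on model assumptions and will shrink toward the population mean where a subject's data are sparse, so shrinkage should be reported with the exposure-response results.
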